## Abstract

**Background:**

The sensitivity of teeth with molar incisor hypomineralization (MIH) can affect children’s quality of life and is a challenging problem for dentists. Remineralizing agents such as sodium fluoride varnish seem to reduce the sensitivity of teeth with MIH, but long-term clinical trials with large samples are still needed for more evidence about its effectiveness as a desensitizing agent before its clinical recommendation.

**Objective:**

This randomized clinical trial aims to compare three treatment interventions for teeth with MIH and hypersensitivity.

**Methods:**

A total of 60 children aged 6-10 years presenting with at least one first permanent molar with sensitivity and no loss of enamel will be randomly assigned to three groups: the control group (sodium fluoride varnish; Duraphat, Colgate); experimental group I (4% titanium tetrafluoride varnish); and experimental group II (a coating resin containing surface prereacted glass-ionomer filler; PRG Barrier Coat, Shofu). The sodium fluoride varnish and 4% titanium tetrafluoride varnish will be applied once per week for 4 consecutive weeks and the PRG Barrier Coat resin will be applied in the first session and the application will be simulated the following 3 weeks to guarantee the blinding of the study. The primary outcome will be sensitivity level measured at different moments (before each material application, immediately after application or simulation, and 1, 2, 4, and 6 months after the last application/simulation) by one examiner using the Wong-Baker FACES Pain Rating Scale, the Schiff Cold Air Sensitivity Scale, and the FLACC (Face, Legs, Activity, Cry, Consolability) scale. As secondary outcomes, parental satisfaction and child self-reported discomfort after the treatment will be measured with a questionnaire prepared by the researcher. The data will undergo statistical analysis and the significance level will be set at 5%.

**Results:**

The project was funded in 2018, and enrollment was completed in November 2019. The recruitment of participants is currently underway and the first results are expected to be submitted for publication in 2022.

**Conclusions:**

If found effective in reducing the patient’s sensitivity long term, these agents can be considered as a treatment choice, and the findings will contribute to the development of a treatment protocol for teeth with sensitivity due to MIH.

**Trial Registration:**

Brazilian Registry of Clinical Trials Universal Trial Number U1111-1237-6720; https://tinyurl.com/mr4x82k9

**International Registered Report Identifier (IRRID):**

DERR1-10.2196/27843

## Introduction

Molar incisor hypomineralization (MIH) is a developmental defect of the enamel that affects one or more permanent molars, often associated with permanent incisors [1]. The affected teeth have lower mineralization, resulting in weaker enamel, which can undergo posteruptive breakdown [2,3]. The prevalence of hypersensitivity in MIH-affected teeth is around 34%, and some children might complain of spontaneous discomfort or pain triggered by thermal or mechanical stimuli [4].

Acute tooth sensitivity can occur when the dentist applies an air jet or performs clinical procedures. However, sensitivity can persist even after local anesthesia administration, resulting in anxiety and behavioral problems during dental treatment [5]. The cause of MIH sensitivity is not entirely clear [6]. One hypothesis is that repeated stimuli might cause a subclinical pulp inflammatory response due to the porosity of the enamel, which facilitates the penetration of bacteria in the dentinal tubules [6,7].

The management of MIH sensitivity represents a major challenge [1,4,7]. Several treatments are available, including the use of fluoride toothpaste, the use of oral care products containing casein phosphopeptides-amorphous calcium phosphate [8,9], and the application of topical sodium fluoride varnish [10-13] with or without laser therapy [14]. Sodium fluoride varnish retains the fluoride close to the teeth for a longer time, resulting in desensitization [15,16]. However, while the use of these agents is empirical, there are no long-term clinical trials with consistent results that evaluate their effectiveness.

The experimental 4% titanium tetrafluoride (TiF_4_) varnish is a promising material for decreasing sensitivity. Several in vitro and in situ studies have shown that TiF_4_ varnish has a greater remineralization effect and reduces enamel demineralization when compared to sodium fluoride varnish (5% NaF) [17,18]. Titanium tetrafluoride (TiF4) reacts with hydroxyapatite and induce a higher deposition of calcium fluoride, forming an acid-resistant layer [19,20].

Recently, a new bioactive technology called surface prereacted glass-ionomer (S-PRG) has been tested on many types of dental materials. It is based on a prereacted fluorosilicate particle with polyacrylic acid, allowing the material to have both biological effects from the glass ionomer cement (fluoride release and recharge) [21-23] and the excellent physical, mechanical, and optical properties of nanohybrid composites. The material also has several other ions in its structure, such as aluminum [24], which is related to sensitivity control. Among materials containing S-PRG, a light-cured bioactive coating resin, the PRG Barrier Coat, can provide immediate and long-term relief for up to 6 months [25].

Because new alternatives for the treatment of tooth sensitivity due to MIH are needed, this randomized clinical trial with parallel arms aims to compare three treatment interventions (5% NaF, 4% TiF_4_, and a light-curing S-PRG–based bioactive coating resin). If these agents contribute to the reduction of patients’ sensitivity, they will be considered a treatment choice. The findings of this study will help inform the development of a treatment protocol for teeth with sensitivity due to MIH.

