### Selection of Participants and Sample Size Calculation

The study participants will be selected from the city of Bauru, São Paulo, Brazil, which has a population of 371,690 inhabitants and a Human Development Index of 0.801. Participants aged 6-10 years will be selected from an epidemiological survey in municipal schools. These schools are located in an urban area, in different zones (north, south, east, and west), and will be selected by a draw according to each zone. In the selected schools, all children aged 6-10 years will be evaluated. Children with potential for inclusion in the research will be referred for a clinical examination at the pediatric dentistry clinic of Bauru School of Dentistry, University of São Paulo, and those that have at least one first permanent molar affected by MIH with hypersensitivity complaint and without loss of structure will be invited to participate. The sensitivity complaint will be confirmed by applying a 1-second air jet at a distance of 1 centimeter from the occlusal surface of the tooth; a score of 2 or 3 on the Schiff Cold Air Sensitivity Scale (SCASS) will be considered as a positive result. Patients with orthodontic appliances, syndromes that involve enamel malformation, or behavioral problems during the clinical examination will be excluded. 

The sample size was calculated considering analysis of variance, performed in SigmaPlot (version 12.3; SPSS Inc), and it was considered a minimally detectable difference of 1 on the SCASS scores between groups. A standard deviation of 0.9 was used based on a previous study [28], α error was 5%, β error was 20%, and a dropout rate of 18% was used, which resulted in a total of 60 children (20 per group). The first 60 children who meet the inclusion criteria will be selected to be part of the study, while others who also present with sensitivity but cannot be included will receive the necessary treatment.

Recruitment will take place from October 2019 to December 2021. After allocation and treatment for 4 weeks, the patients will be followed up for 6 months.

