### Random Allocation

The included patients will be allocated to one of the 3 treatment options by stratified block randomization: (1) the control group (sodium fluoride varnish; Duraphat, Colgate), (2) experimental group I (4% TiF_4_), and (3) experimental group II (S-PRG resin coating; PRG Barrier Coat, Shofu). The randomization sequence will be generated using Microsoft Excel 365 (Microsoft Corp) by an examiner who will not be involved in any of the clinical trial phases. To ensure allocation concealment, the randomly generated sequence will be sealed in opaque envelopes that will be opened only after the child is ready to receive treatment. The randomization procedure will be done per block of 3 children with the same SCASS scores to guarantee similar scores among groups at baseline.

The analysis unit will be the child and will be considered one tooth per child. If more than one permanent first molar has the condition, all will undergo the same treatment so that there is no interference from different treatments and other factors such as saliva, and one tooth will be selected by a draw to be included in the data analysis. The order of treatment among affected teeth in a patient will also be defined by a draw.

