### Treatment Protocol

All children will receive instructions on noncariogenic diet and oral hygiene. Furthermore, the participants will receive an oral hygiene kit with toothbrush and fluoride toothpaste (both Colgate-Palmolive Company). Immediately before treatment, a supervised toothbrushing will be performed with a fluoride-free toothpaste to standardize the treatment phase and to follow the instructions of the S-PRG resin manufacturer. The study risks for participants are minimal and related to the sensitivity due to MIH.

In the control and experimental I groups, the fluoride varnishes will be applied once per week for 4 consecutive weeks. For the experimental II group, the product will be applied the first week and the application will be simulated the following 3 weeks for patient blinding.

All children in the control and experimental I groups will be treated according to the same protocol:

Supervised toothbrushing with fluoride-free toothpaste.Cotton roll isolation of the area.Drying of the tooth using sterile gauze.Varnish application with microbrush according to the manufacturer’s instructions.Instruction of the patient not to eat or drink for 30 minutes and not to brush for at least four hours after application.Reapplication once per week for 3 weeks, following the described protocol.Follow-up.

For the experimental II group, the treatment protocol according to the manufacturer is as follows:

Supervised toothbrushing with fluoride-free toothpaste.Cotton roll isolation of the area.Drying of the tooth using sterile gauze.Material handling within 2 minutes after mixing.Application of a thin layer with the device provided by the manufacturer, then a 3-second wait.Light curing for 10 seconds.Instruct the patient to avoid colored drinks and food for 3 days.Application simulation the following 3 weeks (repeat steps 1-3).Follow-up.

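### The acceptance statement rests on a reduction in sensitivity with no comparator, but three active arms sharing fluoride toothpaste cannot credit a common fall to any product

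*Protocol article*

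**What the plan says.** The Introduction states that the trial "aims to compare three treatment interventions" and then, on condition that the agents contribute to a reduction in sensitivity, that "they will be considered a treatment choice". The Conclusions paragraph of the Abstract repeats the idea: if found effective in reducing sensitivity long term, "these agents can be considered as a treatment choice". Neither sentence refers to a difference from the control varnish, a margin or a named contrast.

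Under Random Allocation, children "will be allocated to one of the 3 treatment options by stratified block randomization": NaF varnish (control), 4% TiF4 varnish or S-PRG coating. No arm is untreated or inert. Under Treatment Protocol, every child gets diet and hygiene instruction and "the participants will receive an oral hygiene kit with toothbrush and fluoride toothpaste". The Introduction counts that toothpaste among the existing options for MIH sensitivity: "Several treatments are available, including the use of fluoride toothpaste".

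For entry, "a score of 2 or 3 on the Schiff Cold Air Sensitivity Scale (SCASS) will be considered as a positive result". Randomisation is done "per block of 3 children with the same SCASS scores to guarantee similar scores among groups at baseline", without saying which SCASS reading is meant. The Data Analysis section plans a two-way repeated measures ANOVA on group and evaluation time, with Tukey comparisons and attention to their interaction.

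**The concern.** The acceptance wording is about reduction; the design can answer only comparative questions. Sensitivity may fall in all three arms for reasons that have nothing to do with the varnish or coating: the supplied toothpaste, better hygiene, repeated professional attention, and the natural course over about seven months. The analysis includes a test of evaluation time, so a significant fall over time is an output that the report will contain. A reader holding it against the acceptance wording could conclude that all three products work, even if none adds anything to the background.

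This matters beyond phrasing. The Abstract ties the finding to developing a treatment protocol, and the Discussion says that TiF4 varnish might reach the market depending on the results.

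**Working it through.** **1. What the trial is sized for.** Inputs from the sample size section: three groups, difference 1 SCASS point, SD 0.9, α 5%, power 80%, dropout 18%. Take one-way ANOVA with two means 1 apart and the third midway, so λ = n × 1² / (2 × 0.9²).
- n = 16 per group: λ = 9.88, power 0.782.
- n = 17 per group: λ = 10.49, power 0.809.

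This gives 17 × 3 = 51 children, and 51 × 1.18 = 60.2, which matches the stated 60. The trial is sized for a difference between groups. Nothing in it is sized, or controlled, for a claim based on a fall within a group.

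**2. What an equal fall would mean.** Suppose each arm falls by the same amount B from background and by P from its product. Each within-arm change is then B + P. The between-arm contrast is (B + P) − (B + P) = 0, whatever P is. The data cannot tell P = 0 from P > 0, yet the acceptance wording can be read as met whenever B + P > 0. Only differences between arms are free of B.

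**3. How easily background alone would look significant (illustration only).** The document gives no value for B. Assume 17 completers in an arm, SD of change 0.9 and a two-sided paired t test at 5%, with noncentrality B / (0.9 / √17):

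| Assumed B | Noncentrality | Chance of a significant fall |
|---|---|---|
| 0.5 | 2.29 | 58% |
| 0.75 | 3.44 | 90% |
| 1.0 | 4.58 | 99% |

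**4. Regression to the mean depends on which reading is the baseline.** Assume an inert product and a rounded 0–3 score with SD 0.9, population mean 1.0 to 2.0 before selection, test-retest correlation 0.5 to 0.85, entry at 2 or more, and 17 per arm. None of these beyond the SD, the entry threshold and the 17 from step 1 comes from the document.
- Screening score used as baseline: mean fall 0.11 to 0.63 points, and a significant within-arm fall in 11% to 84% of trials (33% at mean 1.5, correlation 0.7).
- Separate later reading used as baseline (select on reading 1, compare readings 2 and 3): mean fall 0.00, and the two-sided test rejects in about 5%.

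The document leans towards the second case without settling it. Screening uses an air jet on the occlusal surface only. The Sensitivity Assessment and Primary Outcome sections describe a jet on buccal and occlusal surfaces, read by a blinded examiner before each application.

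**5. The randomised contrast.** In the same inert scenarios a between-arm ANOVA on the follow-up score rejects in about 5%. Selection and shared background affect all arms alike and do not bias it.

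**The case against.** The strongest reply is that the acceptance wording is not a formal decision rule. It is a rationale sentence and an abstract conclusion, with causal language (contribute, effective) and no test or threshold. Nowhere does the document say that a significant time effect establishes effectiveness. The operative text is comparative: the aim, the 1-point difference between groups, the group and interaction terms, and the promise to offer the product with the best result. The Discussion also regards NaF varnish as the gold standard. Much of this stands. The planned analysis already contains the right contrasts, and the flaw is confined to the conclusion attached to them. But causal wording does not rescue that conclusion, because with three active arms causation can be shown only through a difference between arms, and the wording does not ask for one. Nor is NaF a settled benchmark here: the Introduction says that no long-term trials give consistent results for the existing agents.

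Two stronger readings are tempting. One is that selection at SCASS 2 or 3 by itself makes false claims likely, with a quotable error rate. That requires the screening score to be the baseline and inputs that the document does not supply. The other is that the trial can answer only whether TiF4 or S-PRG differs from NaF. The three-arm design with Tukey comparisons also answers TiF4 versus S-PRG.

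It can also be said that the children may already use fluoride toothpaste, so supplying it may change little. The document does not say, and this is one reason why the background fall cannot be sized.

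**Conclusion.** The point holds as a mismatch between the stated basis for acceptance and what the design can show. An equal fall in all arms could be taken to satisfy the acceptance wording without showing that any product works. This follows from the structure alone (three active arms, a shared co-intervention that the document itself lists as a treatment, and no comparator in the wording) and needs no numerical assumption.

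Its size cannot be fixed from the document. The 58% to 99% for an assumed background fall of 0.5 to 1.0 points, and the 11% to 84% from selection if screening is the baseline, show what is possible; they are not estimates for this trial. With a separate pre-application baseline the selection part largely disappears (drift or correlated errors could leave a little), while toothpaste, attention and natural course remain. The active-control design is legitimate and the randomised comparison is sound. This is worth correcting because it changes what the trial may conclude.

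**What to change.** - Reword the acceptance sentences in the Introduction and the Abstract's Conclusions so that claims about a product's effect rest on the randomised between-arm contrasts in SCASS: the group and group-by-time terms, with Tukey comparisons and confidence intervals, including TiF4 versus S-PRG.
- Report the time effect and within-arm falls descriptively, and state that they include background change.
- State that finding no difference between arms does not show that any product is effective, and that a claim of similarity to NaF would need a justified non-inferiority margin. Superiority to NaF need not be the only route to support.
- Name the first pre-application reading, not the screening score, as the baseline.

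The cost is small: no added arm, children or visits, since a reading before each application is already planned. A non-inferiority margin would take some work to justify, and only if that claim is wanted. The real downside is that the trial can no longer call all three products effective on before-after change alone.

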## Methods

### Ethical Considerations

This clinical trial was submitted to and approved by the Research Ethics Committee of Bauru School of Dentistry under CAAE number 14958719.5.0000.5417 and was registered in the clinical studies database (Brazilian Registry of Clinical Trials Universal Trial Number U1111-1237-6720). This protocol follows the SPIRIT (Standard Protocol Items: Recommendations for Interventional Trials) and CONSORT (Consolidated Standards of Reporting Trials) guidelines for randomized trials of nonpharmacological treatments [26].

Participants will be included after their parents or guardians have signed an informed consent form containing detailed information about the research. The children will receive an assent term, with age-appropriate language, explaining how the research will be conducted and that they will be free to accept or reject participation in the study. Participant confidentiality will be guaranteed, and only researchers will have access to the data. At the end of the study, the researchers are committed to offering treatment with the product that demonstrates the best result, regardless of which experimental group the child was in.

### Study Design

This is a double-blind randomized controlled clinical study, conducted with three parallel groups, with a duration of 6 months (Figure 1). The participants and their parents/guardians, as well as the examiners, will not be aware of the group allocation of any patients.

**Figure 1 figure1:**
[figure not shown]
Study Flowchart.

### Examiner Calibration

Examiner calibration will be performed using 35 original photographs of teeth with MIH with different degrees of severity and other developmental enamel defects. The photographs will be evaluated based on the MIH index [27]. All photographs will be reevaluated by the two examiners after 15 days to assess inter- and intraexaminer agreement (κ>0.85).

### Selection of Participants and Sample Size Calculation

The study participants will be selected from the city of Bauru, São Paulo, Brazil, which has a population of 371,690 inhabitants and a Human Development Index of 0.801. Participants aged 6-10 years will be selected from an epidemiological survey in municipal schools. These schools are located in an urban area, in different zones (north, south, east, and west), and will be selected by a draw according to each zone. In the selected schools, all children aged 6-10 years will be evaluated. Children with potential for inclusion in the research will be referred for a clinical examination at the pediatric dentistry clinic of Bauru School of Dentistry, University of São Paulo, and those that have at least one first permanent molar affected by MIH with hypersensitivity complaint and without loss of structure will be invited to participate. The sensitivity complaint will be confirmed by applying a 1-second air jet at a distance of 1 centimeter from the occlusal surface of the tooth; a score of 2 or 3 on the Schiff Cold Air Sensitivity Scale (SCASS) will be considered as a positive result. Patients with orthodontic appliances, syndromes that involve enamel malformation, or behavioral problems during the clinical examination will be excluded. 

The sample size was calculated considering analysis of variance, performed in SigmaPlot (version 12.3; SPSS Inc), and it was considered a minimally detectable difference of 1 on the SCASS scores between groups. A standard deviation of 0.9 was used based on a previous study [28], α error was 5%, β error was 20%, and a dropout rate of 18% was used, which resulted in a total of 60 children (20 per group). The first 60 children who meet the inclusion criteria will be selected to be part of the study, while others who also present with sensitivity but cannot be included will receive the necessary treatment.

Recruitment will take place from October 2019 to December 2021. After allocation and treatment for 4 weeks, the patients will be followed up for 6 months.

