### Data Analysis

Statistical analysis will be performed with SigmaPlot (version 12.3; SPSS Inc). For the WBFPS, SCASS, and FLACC scale, the three groups and evaluation time will be compared by 2-way repeated measures analysis of variance followed by a Tukey test, based on the recommendation of Cohen [31], to allow for interaction analysis between study factors and to avoid an inflated α error. A Spearman correlation test will be performed to determine if there is a significant correlation among the WBFPS, SCASS, and FLACC scale. The significance level will be set at 5%. Poisson regression will be used to assess the influence of IPV, GI, and discomfort on the outcome. The satisfaction of parents/guardians and participants will be analyzed descriptively.

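### Minor: under the usual reading of its own inputs, 60 children support about 15% loss at 80% ANOVA power, not the stated 18%

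*Protocol article*

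**What the plan says.** Under Selection of Participants and Sample Size Calculation, the protocol article states the method ("The sample size was calculated considering analysis of variance, performed in SigmaPlot (version 12.3; SPSS Inc")), the target ("it was considered a minimally detectable difference of 1 on the SCASS scores between groups") and the variability ("A standard deviation of 0.9 was used based on a previous study [28"]). The type I error is 5% and the type II error 20%. The result follows: "a dropout rate of 18% was used, which resulted in a total of 60 children (20 per group"). The section gives no evaluable number per group, no formula for the dropout allowance and no pattern for the three group means.

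Two other sections bear on the point. Data Analysis plans a two-way repeated measures ANOVA "followed by a Tukey test", with no power stated for the pairwise step. Random Allocation forms blocks by baseline sensitivity: "The randomization procedure will be done per block of 3 children with the same SCASS scores". Data Analysis does not mention that score as a factor or covariate.

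**The concern.** A dropout allowance should leave enough children, after the assumed loss, to reach the stated power. Taking 18% from 60 leaves about 49, while whole equal groups with 80% power come to 51. If so, the sentence claims slightly more protection against loss than the sample gives.

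Attrition is a live matter in this trial. Follow-up Examinations removes children whose breakdown reaches dentin or who develop a cavitated lesion, and Results reports that one of the first six children treated was excluded at one month because the tooth was restored elsewhere. Six children cannot estimate a rate, and nothing shows that the 18% leaves such exclusions out. They do show that the margin will be used. A reader of a null result should know what power the trial had at the planned loss.

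**Working it through.** **Inputs.** From the sample size section: three equal groups, difference 1, SD 0.9, alpha 0.05, power 0.80, dropout 0.18, total 60. Assumption, not in the document: means (0, 0.5, 1), the least favourable pattern with a largest difference of 1.

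**Formula.** One-way ANOVA power is the probability that a noncentral F variable with 2 and 3n − 3 degrees of freedom exceeds the 95% point of the central F. The noncentrality is λ = n × Σ(mean − grand mean)² / SD² = n × 0.5 / 0.81.

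**Reproducing the plan's figure.**
- With n not rounded, 80% power is reached at 16.65 per group, 49.9 in total. Then 49.9 / 0.82 = 60.9, so 61, close to the stated 60 but above it.
- With whole groups of 17, 51 × 1.18 = 60.18, which matches 60.
- With 16 per group, 16 / 0.82 = 19.5, so 20 per group and 60 in total, but 16 per group has only 78.2% power.

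The figure is therefore reproduced approximately. The route is not shown, and none of the three delivers 80% power after 18% loss under this pattern.

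**ANOVA power by evaluable number.**

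| Evaluable per group | λ | Power |
|---|---|---|
| 16 | 9.88 | 78.2% |
| 16.4 | 10.12 | 79.3% |
| 17 | 10.49 | 80.9% |
| 20 (no loss) | 12.35 | 87.5% |

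The smallest whole equal group with 80% power is 17, or 51 children.

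**Dropout.**
- 60 × 0.82 = 49.2 children, or 16.4 per group.
- Forty-nine children split 16/16/17 have 78.3% power if the middle-mean group has 17, and 79.5% if an outer group does.
- Loss that 60 children can absorb: 1 − 51/60 = 15.0%.
- Enrolment needed for 18%: 17 / 0.82 = 20.7, so 21 per group, 63 in total. Then 63 × 0.82 = 51.7 evaluable and power is about 81%.

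**Sensitivity to the assumption.** With means (0, 0, 1), λ = n × 0.667 / 0.81. Power is 80.8% at 13 per group and 89.1% at 16, so 60 children would be ample. That pattern would have called for only 13 / 0.82 = 15.9, so 16 per group (48 in total), which suggests that the stated 20 came from the least favourable pattern.

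**Tukey comparison (separate remark).** The critical value is the 95% studentized range point for three groups divided by √2. The noncentrality is 1 / (0.9 × √(1/n₁ + 1/n₂)), and power comes from the noncentral t. With 49 children, power for one pair is 76.2% (16 v 16) or 77.6% (16 v 17). It is 79.1% at 17 per group and 86.2% at 20 per group.

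**Adjusting for baseline SCASS.** With baseline-outcome correlation r, the residual SD is 0.9 × √(1 − r²) and one degree of freedom is lost. At 16.4 per group:

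| Assumed r | ANOVA power | Tukey power, one pair |
|---|---|---|
| 0.2 | about 81% | about 79% |
| 0.3 | about 83% | about 82% |
| 0.5 | about 90% | about 89% |

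The document gives no value of r. These rows show a range, not a prediction.

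**The case against.** The strongest reply is that this is rounding. Without rounding, the plan needs 49.9 evaluable children and has 49.2, and 61 against 60 is ordinary planning tolerance. The pattern of means is also an assumption, and under (0, 0, 1) there is no shortfall. The SD matters far more: at 16.4 per group, SD 0.85 gives 84.0% power and SD 0.95 gives 74.6%. Finally, a one-way calculation is not the power of the planned repeated measures analysis, for which no correlation is given.

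Most of this stands, and it sets the grade. It does not make the sentence right: children come in whole numbers, the groups are specified as equal, and even the unrounded route exceeds 60.

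Three stronger readings are tempting and unsupported:
- **The stated 80% is really 76-78%, because Tukey decides which groups differ.** The protocol states its power for analysis of variance only and promises none for Tukey. Tukey power is below 80% even at 17 per group, so most of that gap is not a dropout effect.
- **The planners multiplied by 1.18 instead of dividing by 0.82.** The numbers fit, but starting from 16 per group and dividing also leads to 60. No formula is given.
- **Baseline adjustment restores 80% power.** That depends on an unknown correlation, which may be low because entry is limited to scores 2 or 3. At r = 0.2 the Tukey figure is still about 79%.

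**Conclusion.** The point holds as a minor correction. Under the least favourable means, 60 children with 18% loss give 78-79.5% ANOVA power instead of 80%. The shortfall is two evaluable children (51 against 49) or three enrolled (63 against 60). The sample covers 15% loss at the stated power.

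This rests on three things: the (0, 0.5, 1) pattern, whole equal groups, and a one-way comparison at a single time point. It gives no reason to doubt the feasibility of the trial or to enrol more children. The lower power of a single Tukey comparison is worth knowing when a null pairwise result is read, but it contradicts nothing in the protocol.

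**What to change.** Keep 60 children and replace the end of the sample size paragraph with wording such as: assuming group means of 0, 0.5 and 1 and SD 0.9, 17 evaluable children per group (51) give 80% power for the ANOVA; 60 children allow 15% dropout at that power, and at 18% dropout power is about 79%. A further sentence may add that a single Tukey comparison of a 1-point difference has about 76-78% power with 49 children.

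In Data Analysis, include the SCASS score used to form the randomization blocks as a factor or covariate in the group comparison. This respects the design and may recover the shortfall; the text should not promise that it does.

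The cost is two or three sentences and one model term. Nobody extra is enrolled, and the stated figures become slightly less favourable. If 80% power at 18% loss is to be kept without relying on adjustment, the alternative is 63 children, 21 per group.
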